## APPENDIX iv.

|                                                                                                 | Before surgery | During surgery (every hour) | End of surgery | Day 1 | Day 2 | Day 3 | Day 4 | Day 5 | Day of hospital discharge | postop Day 90 (Phone call) |
|-------------------------------------------------------------------------------------------------|----------------|-----------------------------|----------------|-------|-------|-------|-------|-------|---------------------------|----------------------------|
| All patients eligible for the study                                                      |                |                             |                |       |       |       |       |       |                           |                            |
| Screening and Randomization                                                              |                |                             |                |       |       |       |       |       |                           |                            |
| Daily screening                                                                                 | X              |                             |                |       |       |       |       |       |                           |                            |
| Demographic data (registry)                                                                     | X              |                             |                |       |       |       |       |       |                           |                            |
| Inclusion/Exclusion criteria                                                                    | X              |                             |                |       |       |       |       |       |                           |                            |
| ARISCAT Score                                                                                   | X              |                             |                |       |       |       |       |       |                           |                            |
| Informed consent                                                                                | X              |                             |                |       |       |       |       |       |                           |                            |
| Randomization                                                                                   | X              |                             |                |       |       |       |       |       |                           |                            |
| Randomized patients                                                                      |                |                             |                |       |       |       |       |       |                           |                            |
| Before Surgery                                                                           |                |                             |                |       |       |       |       |       |                           |                            |
| Demographic data                                                                                | X              |                             |                |       |       |       |       |       |                           |                            |
| History of previous disease                                                                     | X              |                             |                |       |       |       |       |       |                           |                            |
| Physical examination                                                                            | X              |                             |                |       |       |       |       |       |                           |                            |
| SpO 2 in room air                                                                    | X              |                             |                |       |       |       |       |       |                           |                            |
| Spirometry (facultative)                                                                        | X              |                             |                |       |       |       |       |       |                           |                            |
| Chest X-ray (facultative)                                                                       | X              |                             |                |       |       |       |       |       |                           |                            |
| Routine laboratory tests (facultative)                                                          | X              |                             |                |       |       |       |       |       |                           |                            |
| Blood sampling (special markers, facultative)                                                   | X              |                             |                |       |       |       |       |       |                           |                            |
| During Surgery                                                                           |                |                             |                |       |       |       |       |       |                           |                            |
| Respiratory variables                                                                           |                | X                           |                |       |       |       |       |       |                           |                            |
| Hemodynamic variables                                                                           |                | X                           |                |       |       |       |       |       |                           |                            |
| End of Surgery                                                                           |                |                             |                |       |       |       |       |       |                           |                            |
| Protocol dropout?                                                                               |                |                             | X              |       |       |       |       |       |                           |                            |
| Rescue therapy?                                                                                 |                |                             | X              |       |       |       |       |       |                           |                            |
| Anesthesia variables                                                                            |                |                             | X              |       |       |       |       |       |                           |                            |
| Adverse Events (possibly related to RMs)                                                        |                |                             | X              |       |       |       |       |       |                           |                            |
| Surgery variables                                                                               |                |                             | X              |       |       |       |       |       |                           |                            |
| Intraoperative fluid balance/transfusion requirement                                            |                |                             | X              |       |       |       |       |       |                           |                            |
| Continuation of mechanical ventilation after surgery                                            |                |                             | X              |       |       |       |       |       |                           |                            |
| Blood sampling (special markers, facultative)                                                   |                |                             | X              |       |       |       |       |       |                           |                            |
| Follow Up                                                                                |                |                             |                |       |       |       |       |       |                           |                            |
| Physical examination                                                                            |                |                             |                | X     | X     | X     | X     | X     | X                         |                            |
| Actual recovery status (ICU stay, ventilatory support, mobility, bowel function, wound healing) |                |                             |                | X     | X     | X     | X     | X     | X                         |                            |
| SpO 2 in room air                                                                    |                |                             |                | X     | X     | X     | X     | X     | X                         |                            |
| Spirometry (facultative)                                                                        |                |                             |                | X     | X     | X     | X     | X     | X                         |                            |
| Chest X-ray (facultative)                                                                       |                |                             |                | X     | X     | X     | X     | X     | X                         |                            |
| Routine laboratory tests (facultative)                                                          |                |                             |                | X     | X     | X     | X     | X     | X                         |                            |
| Blood sampling (special markers, facultative)                                                   |                |                             |                |       |       |       |       | X     |                           |                            |
| Post-operative fluids/transfusion requirement                                                   |                |                             |                | X     | X     | X     | X     | X     |                           |                            |
| Pulmonary complications (APPENDIX iii)                                                          |                |                             |                | X     | X     | X     | X     | X     | X                         |                            |
| Extra-pulmonary organ failure (APPENDIX iii)                                                    |                |                             |                | X     | X     | X     | X     | X     | X                         |                            |
| Adverse Events                                                                                  |                |                             |                | X     | X     | X     | X     | X     | X                         |                            |
| Date of hospital discharge                                                                      |                |                             |                |       |       |       |       |       | X                         |                            |
| Alive on day 90                                                                                 |                |                             |                |       |       |       |       |       |                           | X                          |
| Hospital-free days on day 90                                                                    |                |                             |                |       |       |       |       |       |                           | X                          |

## APPENDIX v.

### Adverse Events

#### 1. Definitions

An adverse event (AE) is generally defined as any unfavorable and unintended diagnosis, symptom, sign (including an abnormal laboratory finding) syndrome or disease which either occurs during the study, having been absent at baseline, or if present at baseline, appears to worsen. Adverse events are to be recorded regardless of their relationship to the study intervention. With respect to intensity, adverse events are classified as follows:

- Mild                some awareness of symptoms, but easily tolerated;
- Moderate        symptoms causing enough discomfort to interfere with usual activity;
- Severe            incapacitating event causing inability to work or to perform usual activity.

A Serious Adverse Event (SAE) is defined as any experience that suggests a significant hazard or side effect with respect to participants participating in a clinical study. This includes any experience which:

- is fatal or life threatening,
- is permanently disabling, i.e. incapacitating or interfering with the ability to resume normal life patterns,
- requires hospitalisation or prolongation of hospitalisation,
- requires other medically important circumstance (requires medical treatment to avoid one of the above mentioned conditions).

A special form of the SAE is the Suspected Unexpected Serious Adverse Reaction (SUSAR).

Adverse events possibly occurring during this study include but are not limited to unexpected death, inadvertent extubation, development of hemodynamic compromise during a recruitment maneuver or PEEP adjustment, sudden hypoxemia, hypercarbia or a pneumothorax during changes in ventilator setting in either the control or treatment group

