### Nature and extent of the burden and risks associated with participation, benefit and group relatedness

In the intra-operative period, patients will not experience discomfort from either strategy because of general anesthesia. However, systemic hypotension could occur in the higher PEEP group, which would be treated with intravascular volume therapy and/or vasoactive drugs. If the hypothesis proves to be true, patients in the higher PEEP group could benefit from a lower incidence of PPCs. Blood samples will be collected via an existing intravenous catheter or via direct vein puncture, but always in combination with blood sampling for routine care; the amount of additional blood samples can be considered minimal.

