#### 2. Documentation of AEs and SAEs

All adverse events that occur between start of randomized intervention and 90-days follow up have to be immediately documented in the participant's **electronic CRF**. AEs are classified as either serious or non-serious. Details about the clinical symptoms, clinical course and if medical treated, about therapies used should be provided as well as

information about relationship to study intervention, overall intensity and outcome of the adverse event.

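### The adverse event intensity scale rests on felt symptoms and ability to work, so as written it cannot grade events that occur under general anesthesia

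*Protocol*

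**What the plan says.** Appendix v, part 1 (Definitions) of the Protocol sets three intensity grades. The top grade, severe, is an "incapacitating event causing inability to work or to perform usual activity". The lowest, mild, is defined by "some awareness of symptoms, but easily tolerated". The middle grade turns on discomfort that limits what the patient would normally do.

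The same part lists examples of the adverse events that are expected: "unexpected death, inadvertent extubation, development of hemodynamic compromise during a recruitment maneuver or PEEP adjustment, sudden hypoxemia, hypercarbia or a pneumothorax during changes" (the changes meant are those made to the ventilator). Section 8.3 repeats the list. Part 2 of Appendix v sets the window, "All adverse events that occur between start of randomized intervention and 90-days follow up", and says that the record should give "information about relationship to study intervention, overall intensity and outcome of the adverse event". The Summary, under burden and risks, states: "In the intra-operative period, patients will not experience discomfort from either strategy because of general anesthesia".

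No second intensity scale appears anywhere in the Protocol. Seriousness is a separate classification with its own criteria, one of which is a threat to life.

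**The concern.** The study treatment is applied only while the patient is anesthetized, and the harms the Protocol anticipates are mainly physiological or device events at that time. A scale that asks what the patient felt, or whether the patient could work, has nothing to measure there. The field is requested all the same, so something will be entered.

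At stake is whether the intensity field means the same thing across about 90 centers (Section 6.1) and in both arms. Two features of the design make this more than untidy wording:

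- Recruitment maneuvers belong to the higher PEEP strategy. In the lower PEEP arm they appear only as an option at the last rescue step (Section 7.2.2). Maneuver-related events, for which the scale fails most clearly, will therefore fall mostly in one arm.
- Intra-operative data are collected by an investigator who knows the allocation (Section 7.2.1). Improvised grading by someone aware of the arm is a route to differential grading. Nothing in the Protocol shows that this would happen, but nothing in the scale guards against it.

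**Working it through.** No sample size, rate or boundary enters this point, so there is nothing to recompute. The check sets the grade definitions against the situations in which they must be used.

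**Step 1. Which named harms arise in a ventilated patient?** The list has six items. Inadvertent extubation, and hemodynamic compromise during a recruitment maneuver or PEEP change, can occur only in a ventilated patient. Hypoxemia, hypercarbia and pneumothorax are listed together with ventilator changes. Unexpected death is the one item with no such tie. Five of the six therefore belong, on the natural reading, to a ventilated patient. Appendix iv agrees: it schedules a check at end of surgery for events possibly related to recruitment maneuvers.

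**Step 2. Can each grade be assigned in each setting?**

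| Grade | Anchor | Under anesthesia | Awake inpatient | After discharge |
|---|---|---|---|---|
| Mild | Awareness of symptoms | No: no awareness | Yes | Yes |
| Moderate | Discomfort that limits usual activity | No: no discomfort, no activity to limit | Partly: discomfort can be reported, but activity is already limited by the operation | Yes |
| Severe | Event causes inability to work or carry on usual activity | No: the anesthetic causes the inability, not the event | Partly: effect of the event is mixed with that of the operation | Yes |

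The Summary's own statement that patients feel no discomfort during surgery confirms the third column.

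**Step 3. Is the field optional at that time?** No. The window in Appendix v, part 2 opens with the randomized intervention, and overall intensity is among the details to be given. Events during surgery fall inside it.

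**Step 4. What depends on the grade?**

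- Reporting times (Section 8.3; Appendix v, part 3) follow seriousness, with relatedness and expectedness added in Appendix v. Intensity does not enter.
- Forwarding by the SAE manager to the DSMB follows relatedness and expectedness. The DSMB also reviews all events every six months.
- Section 8.2 contains no analysis of intensity and calls everything except the primary outcome exploratory.

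**Step 5. What else records how bad an intra-operative event was?**

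- Section 7.1.2 has desaturation lasting more than 1 minute and, during recruitment maneuvers, systolic pressure below 90 mmHg for more than 2 minutes.
- Section 7.2.2 (Protocol deviation) has low systolic pressure for more than three minutes that does not respond to treatment. Section 7.2.4 records treatment-resistant hypotension as a deviation.
- Section 7.2.4 also records new hypotension, bradycardia and hypoxemia around maneuvers by threshold (present or absent, not graded), together with pressures, saturation, and vasoactive drug type and dose.
- Appendix v asks for clinical course, therapies, outcome, seriousness and a narrative.

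A reviewer can therefore judge a single event. What is missing is a standardized grade that can be tabulated.

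**The case against.** The strongest reply is that little depends on this field. The main intra-operative harms are captured elsewhere by thresholds and durations, and a brief pressure drop and a treatment-resistant one are recorded as different items whatever intensity is entered. The DSMB receives narratives. This stands, and it is why the point is minor. It does not rescue the field itself: the threshold items are present or absent, seriousness has two levels and cannot rank non-serious events, and narratives do not yield a grade comparable across centers.

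Three stronger readings are tempting, and the Protocol does not support them.

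- *Every event under anesthesia becomes severe, so severe counts are inflated.* The definition requires that the event cause the incapacity. Under anesthesia the anesthetic causes it, so the stricter reading is that no grade applies. Any multiplier for inflation would only be the reciprocal of an assumed share of truly severe events, and the Protocol gives no such share.
- *Post-operative inpatients cannot be graded either.* Awake patients can report symptoms and discomfort. The activity and work anchors are confounded by the operation, which makes the scale imprecise there but not unusable.
- *The DSMB's comparison of severe events between arms is lost.* The Protocol specifies no such comparison.

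A fair objection to the remedy is that grading by treatment given makes the grade depend partly on treatment decisions by clinicians aware of the allocation. This stands as a cost. Tying grades to recorded thresholds and durations limits it.

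**Conclusion.** The point holds in a limited form. The Protocol states an intensity scale, asks for it from the start of the intervention, and that scale does not fit most of the harms the same document names. This is a definition fixed in the Protocol, not a detail left to a statistical analysis plan.

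The size is minor. The defect affects one descriptive safety field, chiefly for intra-operative events. The primary analysis, the interim boundaries, expedited reporting and case-by-case safety review are untouched. It is worth correcting because the correction is cheap and because the ungradable events are concentrated in one arm.

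The conclusion rests on two assumptions: that the grades are applied as worded, and that sites have no supplementary grading guidance outside the Protocol. If such guidance exists, the remaining step is to bring it into Appendix v.

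**What to change.** In Appendix v, part 1, add observer-rated intensity definitions for events during anesthesia and the inpatient stay, identical in both arms:

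- mild: transient and resolved without treatment;
- moderate: resolved with treatment;
- severe: persistent or not responding to treatment, or leaving lasting harm.

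Where possible, tie these grades to the thresholds, durations and non-response criteria already in Sections 7.1.2, 7.2.2 and 7.2.4, so that they rest on recorded data. Keep the symptom-based wording for the period after discharge, where it works. Keep seriousness, including threat to life, as a separate field. These definitions classify events for the record only and change nothing in how patients are treated.

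The cost is a few lines of text, a change to the electronic CRF pick-list, and regrading of events already entered from the therapies and narratives that Appendix v already asks for. No new data collection is needed. The remaining drawback is the partial dependence of the grade on treatment decisions made by staff who know the allocation.
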